## Abstract

**Introduction:**

People with aphasia following stroke experience disproportionally poor outcomes, yet there is no comprehensive approach to measuring the quality of aphasia services. The Meaningful Evaluation of Aphasia SeRvicES (MEASuRES) minimum dataset was developed in partnership with people with lived experience of aphasia, clinicians and researchers to address this gap. It comprises sociodemographic characteristics, quality indicators, treatment descriptors and outcome measurement instruments. We present a protocol to pilot the MEASuRES minimum dataset in clinical practice, describe the factors that hinder or support implementation and determine meaningful thresholds of clinical change for core outcome measurement instruments.

**Methods and analysis:**

This research aims to deliver a comprehensive quality assessment toolkit for poststroke aphasia services in four studies. A multicentre pilot study (study 1) will test the administration of the MEASuRES minimum dataset within five Australian health services. An embedded mixed-methods process evaluation (study 2) will evaluate the performance of the minimum dataset and explore its clinical applicability. A consensus study (study 3) will establish consumer-informed thresholds of meaningful change on core aphasia outcome constructs, which will then be used to establish minimal important change values for corresponding core outcome measurement instruments (study 4).

**Ethics and dissemination:**

Studies 1 and 2 have been registered with the Australian and New Zealand Clinical Trial Registry (ACTRN12623001313628). Ethics approval has been obtained from the Royal Brisbane and Women’s Hospital (HREC/2023/MNHB/95293) and The University of Queensland (2022/HE001946 and 2023/HE001175). Study findings will be disseminated through peer-reviewed publications, conference presentations and engagement with relevant stakeholders including healthcare providers, policy-makers, stroke and rehabilitation audit and clinical quality registry custodians, consumer support organisations, and individuals with aphasia and their families.

STRENGTHS AND LIMITATIONS OF THIS STUDYThis research will deliver a comprehensive, fit-for-purpose, quality assessment toolkit for aphasia care after stroke, ready for implementation in the Australian context.This is a world-first pilot of a coproduced minimum dataset in poststroke aphasia services.Our research will establish clinically meaningful benchmarks of change for core aphasia outcome measurement instruments in partnership with key stakeholders including people with lived experience of aphasia who will be involved in all phases of the research.This pilot study is limited to the Australian metropolitan public healthcare context, which may limit translation to other geographical and care settings.Future studies employing the Meaningful Evaluation of Aphasia SeRvicES minimum dataset could integrate behavioural and imaging data to gain a fuller understanding of factors influencing aphasia recovery.

## Introduction

Globally, 12.2 million people experience a stroke annually.^1^ Up to 40% of stroke survivors initially experience aphasia,^2^ which affects the ability to produce and understand language. Language underpins family, social and vocational interactions and accordingly, aphasia is associated with significant psychosocial impacts^3^ and poor health-related quality of life.^4^ Speech and language therapy for aphasia is effective^5–7^ and meta-analysis of large individual patient datasets reveals that people with aphasia who receive intensive, frequent, and tailored speech and language therapy achieve better outcomes.^8^ In clinical practice, however, people with aphasia receive limited therapy^9–11^ and finite clinical resources may not be used efficiently due to a lack of understanding of which treatments work best and for whom.^12 13^ The delivery of high-value, personalised aphasia treatment that makes the best use of available resources requires an understanding of the characteristics of people with aphasia (sociodemographic factors, stroke type or severity and aphasia characteristics), the type and quality of care they receive, and the outcomes they desire and achieve. Currently, data to support understanding of aphasia care and outcomes are not routinely collected^14 15^ and there are few benchmarks of patient-perceived therapy success to indicate when meaningful change has occurred.^16^

Health service monitoring is essential to the delivery of efficient, high-quality and safe healthcare.^17^ Minimum datasets (standardised sets of variables) and core outcome sets (COS) (agreed outcomes and measurement instruments) are often collected within health services to enable benchmarking and drive quality improvement.^18^ At an individual patient level, the routine collection of valid and reliable data can inform treatment decision-making and support the provision of personalised care.^19^ At a service and/or population level, analysis of routinely collected data can provide insights into trends in quality of care and patient outcomes.^19^ Consequently, routinely collected data can inform targeted quality improvement initiatives to reduce variation in patient care, increase alignment with clinical practice guidelines, optimise patient outcomes and support the development of policy to address the needs of patients and communities.^19–21^

In Australia, three national systems for stroke service monitoring exist, however, few aphasia-specific data variables are collected. The Australian Clinical Stroke Registry (AuSCR) aims to monitor and improve the quality of acute stroke care,^22^ collecting patient demographics, type of stroke and clinical indicators of prioritised stroke management (eg, receipt of stroke unit care and swallowing assessment^23^) on consecutive admissions to participating hospitals. While the AuSCR is driving improvements in stroke care in Australia,^24^ the only aphasia-specific information collected is the International Classification of Diseases code for aphasia.^25^ In addition to the AuSCR, the Stroke Foundation National Audit Programme monitors and measures acute and rehabilitation care against the Australian Clinical Guidelines for Stroke Management, using a retrospective audit to inform quality improvement and advocacy.^22^ Currently, only three quality measures relevant to aphasia are collected in the audit: the identification of speech/communication deficits and aphasia; assessment by a speech pathologist; and, identification of management strategies for those identified to have aphasia.^26^ Finally, the Australasian Rehabilitation Outcomes Centre (AROC) dataset aims to drive quality and outcome improvements in rehabilitation through the collection of inpatient rehabilitation data. AROC captures the number of minutes of speech or language therapy provided, but there are no aphasia-specific variables included in this dataset.^27^ A consistent and comprehensive approach to aphasia service monitoring is needed to drive targeted improvement in quality of care and patient outcomes.

### A comprehensive quality assessment toolkit for aphasia care after stroke: the MEASuRES minimum dataset

The MEASuRES (Meaningful Evaluation of Aphasia SeRvicES) minimum dataset was developed in partnership with researchers, clinicians and people with aphasia and their families, to address the gap in routine aphasia-specific data collection and reporting. MEASuRES (box 1) comprises four elements (sociodemographic characteristics, quality indicators, treatment descriptors, outcome measurement instruments) and builds on three international multistakeholder initiatives to standardise aphasia data and outcome collection and description: the DESCRIBE reporting standards project (DESCRIBE^28^), the Research Outcome Measurement in Aphasia COS (ROMA COS^29^) and the International Population Registry for AphasIa after StrokE (I-PRAISE^30^).

Box 1Data items included in the measures minimum datasetSociodemographic characteristics^28^
Person with aphasia.Age.Biological sex.Years of education.Language of assessment and treatment.Primary language spoken at home.Languages used.History of condition known to impact communication or cognition.History of previous stroke.Lesion hemisphere.Time since onset of aphasia.Conditions arising from the neurological event.Communication partner.Age.Biological sex.Relationship to person with aphasia.Quality indicators^36^
A screener and/or assessment is completed to determine if communication impairment (including aphasia) is present.A valid and reliable standardised assessment is conducted to determine aphasia severity.Information about aphasia is provided to the person with aphasia.Information about aphasia is provided to the person with aphasia’s primary carer/communication partner.Information about support is provided to the person with aphasia’s primary carer/communication partner.The primary carer/communication partner of the person with aphasia is provided with communication partner training.Individualised recommendations for communicating with the person with aphasia are provided to the treating team.There is training for staff in supported communication for aphasia.Goal setting is undertaken in partnership with the person with aphasia and their significant others.The person with aphasia receives person-centred/family-centred care.The person with aphasia receives speech and language therapy.Treatment descriptors^30^
Treatment setting.Treatment target.Therapeutic approach.Treatment type.Number and duration of treatment sessions provided.Delivery mode.OutcomesResearch Outcome Measures in Aphasia Core Outcome Set.^29 68^
The Western Aphasia Battery-Revised (Language).The Scenario Test (communication).Stroke and Aphasia Quality of Life Scale-39g (QoL).The General Health Questionnaire-12 (emotional well-being).Minimal important change.^44^
Anchor ratings for each construct (language, communication, QoL, emotional well-being).

### Sociodemographic characteristics

People with aphasia are a heterogeneous population, which presents challenges in prognostication, treatment prescription and implementation of research evidence within clinical contexts. Factors such as age, sex, stroke severity, time poststroke onset, lesion site and size, aphasia type and severity, and comorbidities are likely to impact recovery and treatment outcomes.^5 31^ Social determinants of health (eg, education) are hypothesised to impact aphasia outcomes, however, research in this area is limited^32^ and these factors are generally under-reported in aphasia research.^28^ The DESCRIBE project established internationally agreed minimum reporting standards for participant characteristics in aphasia research, in partnership with multidisciplinary researchers, clinicians and journal editors.^28^

### Quality indicators of clinical processes of care

Clinical guidelines present recommendations for important processes of care (eg, assessment, therapy, education). Guideline adherence can serve as indicators of the quality of care provided (ie, quality indicators).^33^ Associations between adherence to processes of care and improved outcomes have been documented for acute stroke care^34^ and stroke rehabilitation.^35^ However, there is currently no systematic means of determining the quality of aphasia care. A set of quality indicators for poststroke aphasia services has been developed in partnership with clinicians, researchers and people with aphasia and their significant others.^36^ These quality indicators are based on strong research evidence and processes of care identified as being important to stakeholders.

### Treatment descriptors

The I-PRAISE^30^ includes a protocol for the documentation of aphasia treatment delivery. Information regarding treatment types, methods of delivery and treatment dose are required to inform an understanding of poststroke aphasia treatments.^12 37 38^ These treatment descriptors would support the identification of outcome predictors,^12^ however, they are not routinely collected.

### Core outcome measurement instruments

The outcomes achieved by people with aphasia after treatment are defined by change scores on standardised measurement instruments. The ROMA COS defines an internationally agreed standardised protocol for measuring treatment outcomes. The four measurement instruments included in the ROMA COS—Western Aphasia Battery: Revised,^39^ The Scenario Test,^40^ Stroke and Aphasia Quality of Life Scale-39g (SAQOL-39g)^41^ and General Health Questionnaire-12^42^—map directly to constructs that people with aphasia, their families, clinicians and researchers have identified as being essential to understanding aphasia and its consequences (ie, language, communication, quality of life, emotional well-being).^43^ The ROMA COS is designed for use in aphasia research and the feasibility and acceptability of its routine use in clinical settings requires evaluation.

### Interpretation of treatment success: minimal important change

Treatment success cannot be determined by change on standardised outcome measurement instruments alone.^16^ To understand if aphasia treatments are successful from the patients’ perspective, there is a need for objective benchmarks which quantify clinically meaningful changes.^12 16^ These perspectives, alongside outcome measurement change scores for the individual patient, can be used to establish minimal important change (MIC) values.^44^ MIC is the smallest change in the outcome measurement score, in the construct to be measured, which patients perceive to be important.(45p. 408) MIC values have been proposed as a method of interpreting outcomes from the patient perspective and may be an indicator of whether treatment was successful, should continue, or be stopped, delayed, or changed.^46^ MIC bridges the gap between statistical significance of an individual test score and its clinical importance and will facilitate interpretation of individual outcome measurement scores, supporting clinicians to provide high-quality person-centred care,^16^ as well as allowing comparison of treatment responder rates across healthcare facilities.

There are few existing MIC values for aphasia measurement instruments. Guo *et al*
47 conducted an estimation study with 78 stroke survivors with and without aphasia, and included both the English and Mandarin versions of the SAQOL-39g. The SAQOL-39g (included in our minimum dataset) was completed by 34.6% of the participants (n=27). One-point improvement on the Modified Rankin Scale,^48^ a measure of disability rather than quality of life, was used as the threshold of clinically meaningful change to establish the MIC values. There are no known MIC values for the other outcome measurement instruments of the MEASuRES minimum dataset.^16^

## Aims

Our objective is to deliver a comprehensive quality assessment toolkit for aphasia care after stroke. Specifically, we aim to:

Evaluate the use of the MEASuRES minimum dataset in clinical practice (studies 1 and 2).Establish MIC values for core aphasia outcome measurement instruments, informed by stakeholder perspectives of meaningful change (studies 3 and 4).

## Methods and analyses

A comprehensive quality assessment toolkit for aphasia care after stroke will be delivered in four studies (see figure 1 for overview). Studies 1, 2 and 4 will involve speech pathology clinicians collecting components of the MEASuRES minimum dataset and patient perceptions of change alongside routine hospital care. These data will be collected for 200 participants with aphasia throughout the continuum of care across participating health service sites between January and August 2024. The sample size was informed by recommendations for conducting and reporting MIC studies,^46^ aphasia admission rates at each of the participating sites, and power calculations for subgroup analyses for studies 1 and 4. In conjunction with the multicentre study, an expert panel of stakeholders will establish a threshold of meaningful change in study 3. Data collection for study 3 occurred across April and May 2023. Recruitment processes and data analysis for each study are detailed below. Together, the four studies will provide preliminary information about the acceptability and feasibility of using the MEASuRES minimum dataset in routine clinical care. Embedded processes will allow exploration of where, when, and why components of the minimum dataset are not or cannot be collected to inform future refinement and scaling of the minimum dataset.

**Figure 1 F1:**
[figure not shown]
Four linked studies will deliver a comprehensive quality assessment programme for aphasia care after stroke. < Figure 1 Four linked studies will deliver a comprehensive quality assessment programme for aphasia care after stroke >

### Patient and public involvement

Two consumer investigators (KM and PM) and a research advisory group are involved with the project. The consumer investigators with lived experience of aphasia provide expert guidance, feedback and oversight across the project, including contributions to the project design, funding applications and development of the research protocol. The research advisory group comprises people with aphasia (n=3), family members (n=2) and speech pathologists (n=2). The advisory group has contributed to recruitment strategies, study procedures and participant-facing materials. Contributions will continue through interpretation and codissemination of findings through peer-reviewed journal articles and conference presentations. Research advisory group members are remunerated, commensurate with Health Consumers Queensland guidelines,^49^ to convene quarterly, and as needed, to complete specific tasks. Consumer and community involvement will be reported in line with the Guidance for Reporting Involvement of Patients and the Public(GRIPP2) long-form checklist^50^ in future publications.

### Development of the measurement tool

The measurement tool will be used to collect standardised information about people with aphasia, aphasia care and aphasia outcomes in routine clinical care. The development of the measurement tool involves piloting the MEASuRES minimum dataset in clinical practice (study 1) and an embedded process evaluation (study 2).

### Study 1: piloting the MEASuRES minimum dataset

The aim of this study is to administer the MEASuRES minimum dataset in clinical settings to describe participant characteristics, and the delivery and outcomes of poststroke aphasia services. The minimum dataset will be administered by speech pathologists alongside routine clinical care.

### Study design and setting

This multicentre observational pilot study will be conducted in a convenience sample of five Australian publicly funded, metropolitan, tertiary health services providing stroke care: Metro North Hospital and Health Service (Queensland), St Vincent’s Hospital Melbourne (Victoria), Monash Health (Victoria), Sir Charles Gairdner Osborne Park Health Care Group (Western Australia) and Fiona Stanley and Fremantle Hospital Group (Western Australia).

### Participants and sample size

People with aphasia (n=200) who meet the following eligibility criteria will be invited to participate: (1) admitted to a participating health service site; (2) new onset of aphasia caused by a new acute stroke, (3) aged ≥18 years and (4) has capacity to consent by self or with a proxy.

### Recruitment and consent

Patients admitted to participating health service sites with a new acute stroke will be screened for eligibility by clinical speech pathologists. Stroke diagnosis will be determined by the treating stroke physician. Eligible participants will be provided with written, aphasia-friendly participant information and consent forms describing the project, its aims and the research activities. Speech pathologists will provide communication support throughout the consenting process.

Capacity to consent: Speech pathologists working within the health service sites will determine a potential participant’s capacity to consent. Following a discussion about the study using appropriate supported communication techniques, prospective participants will be asked a series of yes/no questions about the study to establish if they have understood the information presented. Patients who answer all questions correctly will be considered to have capacity to consent.

Consent via proxy: If a prospective participant agrees to participate but is not able to demonstrate capacity to provide informed consent at the time of recruitment, a proxy will be invited to consent on their behalf (Queensland and Victorian sites only). In such cases, treating clinicians will continue to monitor the participants’ recovery and will provide further opportunities for the participant to provide their own consent. Patients admitted to Western Australian sites who are unable to demonstrate capacity to consent will be ineligible to participate, in accordance with Western Australian Department of Health legislation.

### Data collection and management

The minimum dataset variables will be collected by speech pathologists using a purpose-built REDCap database.^51^ The continuity of speech pathologists collecting data will be dependent on usual care practices and service structure at each health service site. There will be a minimum interval of two weeks between administrations of aphasia outcome measurement instruments, which is longer than the minimum test–retest reliability assessment interval for most measurement instruments.^41 52^ In instances where elements of the minimum dataset are unable to be collected, reasons for missing or incomplete data will be recorded. Routine data validation will be undertaken to monitor completeness of data and identify invalid data entries. Data quality and completeness will be enhanced by using the logic checks, mandatory fields and duplicate report flagging tools.

### Planned analyses

Data quality and completeness will be summarised using descriptive statistics. For each variable in the minimum dataset, the proportion completed will be calculated to determine patterns of missing, incomplete or invalid data. Missing data will be handled in accordance with the processes outlined in existing guidelines.^53 54^

Similarly, descriptive statistics will be used to summarise patient characteristics, adherence to quality indicators, treatment descriptors and scores on aphasia outcome measurement instruments. Adherence to quality indicators will be defined as the proportion of eligible episodes of stroke in which the indicator was provided, estimated overall and at the hospital level. We will also summarise the total number of indicators provided per episode at each hospital. Associations between patient characteristics, adherence to quality indicators and aphasia outcomes will be determined using multilevel regression models, adjusted for clustering effect within the hospital. The type of regression models to be used for analysis will depend on the nature and distribution of the outcome variables. All regression models will also be adjusted for covariates, including age and baseline scores on the aphasia outcomes and other covariates based on data collected.^53^

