### Data collection

As part of study 1, the ROMA COS will be administered prior to and after usual care aphasia intervention, with a minimum interval of 2 weeks. When consenting for study 1, participants will be provided with written, aphasia-friendly participant information and consent forms describing the research activities associated with study 4. Speech pathologists will provide communication support throughout the consenting process. With the second administration of the ROMA COS, both participant groups (people with aphasia and clinicians) will additionally rate perceived change in language, communication, quality of life and emotional well-being on corresponding anchor scales (figure 2). The second ROMA COS and anchor scales will be collected prior to discharge from inpatient care at the participating health service site. In instances where this is not feasible, outpatient follow-up will be undertaken, following a flexible approach to delivery mode and assessor in line with site-specific agreements.

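### Eligibility fixes quality indicator 1 near 100%, and the study's own WAB-R can inflate indicator 2, so neither can be read as usual-care adherence

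*Protocol article*

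**What the plan says.** The Study 1 section on planned analyses in the protocol article gives the definition: "Adherence to quality indicators will be defined as the proportion of eligible episodes of stroke in which the indicator was provided", estimated overall and at hospital level. It adds: "We will also summarise the total number of indicators provided per episode at each hospital". Adherence then enters multilevel regression models with the aphasia outcomes, adjusted for age and baseline outcome scores among other covariates.

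Box 1 lists 11 quality indicators. The first is "A screener and/or assessment is completed to determine if communication impairment (including aphasia) is present". The second is "A valid and reliable standardised assessment is conducted to determine aphasia severity".

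Under Participants and sample size, entry requires "new onset of aphasia caused by a new acute stroke". Under Recruitment and consent, patients with a new acute stroke "will be screened for eligibility by clinical speech pathologists".

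Box 1 also makes the WAB-R part of the dataset, as the language measure of the ROMA core outcome set. The Study 4 section on data collection says that, within Study 1, "the ROMA COS will be administered prior to and after usual care aphasia intervention, with a minimum interval of 2 weeks". Speech pathologists administer the dataset during routine care. The section on core outcome measurement instruments describes the ROMA set as a research set whose routine clinical use has still to be evaluated.

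The article does not say whether an assessment done for the study counts towards indicator 2.

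**The concern.** An adherence figure is meant to describe what the service does. For indicator 1, the patients who would count as failures are those whose communication was never checked. They are unlikely to be recognised as having aphasia, and so unlikely to enrol. For indicator 2, the study supplies a test that could satisfy the indicator it sets out to observe.

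This matters because Study 1 aims to describe how aphasia services are delivered, and the article expects site-level evidence-practice gaps to inform later quality improvement. A real gap in screening would not show at all. A gap in severity assessment could be partly or wholly hidden, and hospitals could appear to differ on indicator 2 only because they completed the study test at different rates.

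**Working it through.** The article states no adherence figure, so there is none to reproduce. It also gives neither a usual-care rate for any indicator nor an expected WAB-R completion rate. All rates below are assumptions, shown over a range.

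**Indicator 1.** Enrolment requires identified aphasia, and speech pathologists do the eligibility screening. Identifying aphasia involves some screener or assessment, and the indicator asks for no more than that. Hence P(indicator 1 met | enrolled) is about 1, whatever the rate among all stroke admissions.

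**Indicator 2.** Let u be the proportion of episodes with a usual-care severity assessment and c the proportion with a completed study WAB-R. If study tests count:

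- observed rate = u + c − uc under independence;
- bounds for any dependence: max(u, c) to min(1, u + c).

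Observed rate under independence, with the inflation over u in percentage points:

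| u | c = 0.5 | c = 0.7 | c = 0.9 | c = 1.0 |
|---|---|---|---|---|
| 0.1 | 55% (+45) | 73% (+63) | 91% (+81) | 100% (+90) |
| 0.3 | 65% (+35) | 79% (+49) | 93% (+63) | 100% (+70) |
| 0.5 | 75% (+25) | 85% (+35) | 95% (+45) | 100% (+50) |
| 0.9 | 95% (+5) | 97% (+7) | 99% (+9) | 100% (+10) |

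**Hospital comparison.** Take u = 0.3 at both hospitals, with c = 0.5 at one and 0.9 at the other.

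- Independence: 0.3 + 0.5 − 0.15 = 65% against 0.3 + 0.9 − 0.27 = 93%, a gap of 28 points.
- Greatest overlap at both: 50% against 90%, a gap of 40 points.
- Least overlap at both: 80% against 100%, a gap of 20 points.

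The usual-care rates are equal, so the whole gap comes from study completion.

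**Per-episode total.** Two of 11 indicators (18%) are affected. The mean shift is (1 − u1) + c(1 − u2), where u1 and u2 are the usual-care rates of the two indicators. It cannot exceed 2.

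- u1 = 0.9, u2 = 0.5, c = 0.5: 0.10 + 0.25 = 0.35 indicators.
- u1 = 0.5, u2 = 0.1, c = 1.0: 0.50 + 0.90 = 1.40 indicators.

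Indicator 1 adds nearly the same amount at every hospital. It does not create differences between hospitals in the total, though it cannot reveal real ones either.

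**Association models.** Indicator 1 has almost no variation, so its own association with outcome could hardly be estimated. In a WAB-R model adjusted for baseline WAB-R, every patient with an observed baseline would have indicator 2 = 1 if study tests count, so its association could not be estimated among those patients.

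**The case against.** The strongest reply is that the article never says the study WAB-R satisfies indicator 2. Box 1 labels that test as a language measure, not a severity measure. Item-level scoring could sit in the full protocol or the REDCap specification, neither of which is shown. This stands: for indicator 2 the inflation is conditional on study tests being counted. It does not remove the need for a rule, because usual-care and study-prompted assessments cannot be separated at analysis unless the distinction was recorded at collection.

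A reader might infer that both indicators are met automatically and that the total therefore says nothing about care. The documents do not support that. Indicator 2 is affected only where the WAB-R is completed. The Study 1 section on data collection and management expects some items to go uncollected, and whether the test is feasible in routine care is one of the pilot's questions. Nine indicators are untouched. Because adherence is reported indicator by indicator, a ceiling on indicator 1 would be visible, and the article does not say that each indicator will be modelled separately.

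It can also be said that eligible episodes are not expressly equated with enrolled participants. That is true, but the patient-level data described are those of the participants, and no screening record of all stroke admissions is described. Finally, this is a pilot concerned with feasibility. That tempers the consequences but leaves the stated aim of describing service delivery.

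**Conclusion.** The concern holds in two parts of different strength. Indicator 1 is near 100% among enrolled patients because of the eligibility rule. This follows from the entry criteria alone and needs no assumed rate. Indicator 2 is inflated to the extent that the study WAB-R is completed and counted. For usual-care rates of 10% to 90% and completion of 50% to 100%, the inflation is 5 to 90 points under independence. Unequal completion between sites can distort hospital comparisons.

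The total is biased upward, not void. The shift is at most 2 of 11 indicators, and 0.35 to 1.4 for usual-care rates of 0.5 to 0.9 (indicator 1) and 0.1 to 0.5 (indicator 2) with completion of 0.5 to 1.0. A larger-looking illustration is tempting: with every indicator at 60%, the total would read 9 × 0.6 + 2 = 7.4 instead of 11 × 0.6 = 6.6, or 67% instead of 60%. That is a ceiling. It needs one common delivery rate, complete WAB-R data and every study test counted, and the documents give none of these.

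**What to change.** In the Study 1 planned analyses:

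- State that indicator 1 is at ceiling by eligibility, and do not report it as adherence. Take it from all new acute stroke admissions only if an approved screening record exists. The article describes none, and using data on patients who did not consent could need further ethics approval.
- Add one REDCap item recording whether the severity assessment was, or would have been, done as usual care, or was done only for MEASuRES. Count only the former towards indicator 2 and report study-prompted assessments separately. In the example with u = 0.3, indicator 2 would then read 30% at both hospitals, if clinicians answer accurately.
- Do not simply exclude every study WAB-R. A site that would have used the WAB-R anyway has little reason to test twice, and its adherence would be understated.
- Report the per-episode total, and any association model that uses it, with and without these two indicators.

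The cost is some wording, one extra field that relies on the clinician's judgement of what would have happened, and an alternative total of nine indicators beside the full one. The field must be in place while data are being collected, because the information cannot be reliably reconstructed later.
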